### Training programme for healthcare professionals

Several meetings with the participating health, educational and maternal-child centres have taken place to plan and finalise the project organisation. Profs [name] and [name] of the University of Reading (UK) have adapted the Dialogic Book-Sharing programme that they developed and have successfully previously trialled in South Africa and the UK [17, 48–50, 60], specifically for the current project. The core feature is that parents are trained in how to support their child’s interest and active engagement, rather than simply ‘reading’ to their child. Responsiveness is emphasised that is sensitive to the child’s developmental capacity and experience, as well as the importance of a positive encouraging approach. The intervention is being delivered in centres by local staff who, over a 2-day training course, have been trained (by [name] of University of Parma) to act as facilitators. Participants receive ongoing supervision from LM and [name]. In accordance with the literature (e.g. [96]), the supervision sessions help to ensure fidelity with programme delivery (see details below in ‘Measures’). The intervention programme is delivered within each centre in Italian, using PowerPoints and embedded demonstration videos. The course is structured into four, weekly, meetings of the parents lasting 90 min each, which take place at the health, educational and maternal-child centres.

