### Study design

This is a multicentre, two parallel arms, single blinded randomised controlled superiority trial, with a 1:1 arms allocation ratio. The study followed the SPIRIT reporting guidelines (Supplementary File).

Within each health, educational and maternal-child centres, parent–child dyads are randomly assigned by local staff to either the index group or the control condition based on a randomisation list compiled using random blocks algorithm. The index group receive the DBS intervention immediately, and the control group enter a waiting list and receive the DBS intervention after the final study assessment. The local staff, not involved in the participant treatment and blinded to treatment allocation, collect the baseline data during an interview before randomisation and again after the four group sessions. A follow-up evaluation is to be carried out 6 months after the end of the training.

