### Sample size estimation

The sample size was calculated based on the difference of the number of words between the two study groups (index and control group) at post-test. In the Dowdall meta-analysis, the average effect size for expressive language adjusted for baseline pre-test value was 0.41. Taking this value as the reference to compute the sample size for our study, assuming a *t*-test for independent samples, a two-sided 5% significance level, a sample size of 190 (95 in each groups) will provide a power of at least 80% (PASS 2021).

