### Statistical analysis plan

Descriptive statistics will be performed on socio-demographic and baseline child cognitive-behavioural variables using summary statistics such as mean, standard deviation, median and interquartile range. Comparison of test scores measure, derived as combination of individual score items, at post-test between the two groups will be performed using a linear mixed model accounting for baseline (pre-test) test scores values and a random term to account for recruitment centre effect. Individual items measured on an ordinal scale will be compared using cumulative link models for ordinal measures. Results will be reported as effect estimates and corresponding 95% confidence intervals. All tests will be two-sided and will be evaluated assuming a 5% significance level. This analysis will be performed by an independent statistician, blinded for the treatment allocation. The statistician will report to the Data Monitoring Committee. Data will be analysed based on intention to treat principles. A sensitivity analyses will also be performed, excluding not-adherent participants from the analyses.

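### Excluding non-adherent participants is, in a wait-list trial, likely to remove dyads from the DBS arm only, so this sensitivity analysis is not protected by randomisation and may overstate the effect

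*Protocol article*

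**What the plan says.** The Statistical analysis plan section of the protocol article sets the main principle: "Data will be analysed based on intention to treat principles". It then adds: "A sensitivity analyses will also be performed, excluding not-adherent participants from the analyses". Test scores are compared with "a linear mixed model accounting for baseline (pre-test) test scores values and a random term to account for recruitment centre effect". The same section assigns the analysis to an independent statistician who is blinded to allocation.

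Under Study design, "the control group enter a waiting list and receive the DBS intervention after the final study assessment". The section on the training programme describes what an index family is asked to attend: "The course is structured into four, weekly, meetings of the parents lasting 90 min each". Parents are also advised to practise at home between sessions and to continue for six months afterwards. The article does not say what counts as non-adherent.

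**The concern.** Until the final assessment only the index arm has sessions and home practice to adhere to. Excluding the non-adherent therefore filters one arm and leaves the other whole. The filtered DBS arm contains families who were able and willing to attend. The control arm still contains the families who would not have attended had they been offered the course. If those two kinds of family differ in expected child vocabulary, the analysis shows a difference even when DBS does nothing. Baseline score and centre are the only adjustments named, and they need not capture parental engagement.

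A sensitivity analysis is meant to test whether the main result is robust. This one estimates something different, with a selection component added, so agreement with the intention-to-treat result would be weak reassurance and a larger estimate could be mistaken for confirmation.

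There is also a practical point on blinding. Even with coded arms, an exclusion flag that occurs in only one arm shows the statistician which arm is DBS.

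**Working it through.** **Inputs from the protocol article.** Effect size 0.41, two-sided 5%, independent-samples t-test, 95 per group, power at least 80% (Sample size estimation); 1:1 allocation (Study design); adjustment for baseline score and centre (Statistical analysis plan).

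**Reproducing the planned size.** Normal approximation: n = 2 × (1.960 + 0.842)² / 0.41² = 93.4, so 94 per arm. The exact t-test gives 94.35, rounded up to 95 per arm, with power 80.3%. The stated figure is reproduced and is not in question.

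**Assumed inputs, because the article gives neither:**
- f, the share of DBS dyads that are non-adherent: 10%, 20% or 30%.
- g, the outcome gap in SD between dyads who would and would not adhere, after baseline adjustment and with no DBS effect: 0 to 0.5, with -0.3 as a reverse case.

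**Bias.** Let A and N be the expected outcomes of would-be adherers and non-adherers without DBS, so g = A - N. Randomisation gives both arms the same mix. After exclusion the DBS mean is A and the control mean is (1 - f)A + fN. The difference under no effect is f(A - N) = f × g.

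**Null rejection rate.** With 95(1 - f) DBS dyads, 95 controls and SD = 1, SE = √[1/(95(1 - f)) + 1/95]. The two-sided rejection rate is Φ(bias/SE - 1.96) + Φ(-bias/SE - 1.96). Centre effects are ignored.

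Worked case, f = 20% and g = 0.3: bias = 0.06; SE = √(1/76 + 1/95) = 0.154; bias/SE = 0.39; rejection = 0.0582 + 0.0094 = 6.8%.

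| f | g | Bias (SD) | Null rejection |
|---|---|---|---|
| 10% | 0.2 | 0.02 | 5.2% |
| 10% | 0.5 | 0.05 | 6.3% |
| 20% | 0.2 | 0.04 | 5.8% |
| 20% | 0.3 | 0.06 | 6.8% |
| 20% | 0.5 | 0.10 | 10.0% |
| 30% | 0.2 | 0.06 | 6.6% |
| 30% | 0.5 | 0.15 | 15.5% |
| any | 0 | 0 | 5.0% |
| 10-30% | -0.3 | -0.03 to -0.09 | 5.5-8.7%, mostly against DBS |

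**How much of a gap survives baseline adjustment.** If a stable raw gap is already present at pre-test and the pre/post correlation is r, about (1 - r) of it remains. The article does not give r; take 0.6-0.9 as an assumption. With f of 20-30% and raw gaps of 0.3-0.5 SD, the bias runs from 0.2 × 0.3 × 0.1 = 0.006 SD to 0.3 × 0.5 × 0.4 = 0.06 SD. Allowing for the smaller residual SD, √(1 - r²), null rejection is 5.1-7.6%.

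**If DBS works, but only in adherers (0.41 SD), with f = 20% and g = 0.3.** Intention to treat targets 0.8 × 0.41 = 0.328. Exclusion targets 0.41 + 0.06 = 0.47. Dividing the intention-to-treat effect by the adherent share gives 0.328 / 0.8 = 0.41, whatever g is. Of the 0.142 SD between exclusion and intention to treat, 0.082 is the legitimate difference between the two targets and 0.06 is selection.

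**The case against.** The strongest reply is that inference is already protected. Intention to treat is the stated principle, the exclusion is only a sensitivity analysis, and the article rests no claim on it. That stands: the main comparison, its error rate and the sample size are untouched.

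A reader might infer that exclusion certainly biases towards DBS. The article does not support this. The sign follows g, which is not given. Engaged parents may well have children with larger vocabularies, but parents worried about a slow talker could be the keener attenders.

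A reader might also settle on a spurious gain of 0.06-0.15 SD, which is 15-37% of 0.41. That needs 20-30% non-adherence and a whole gap of 0.3-0.5 SD surviving adjustment for a pre-test score taken shortly before a four-week course. Nothing in the article establishes either.

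Next, one-arm exclusion is an inference, because adherence is undefined here and may be defined in a fuller document. A rule that counted missed assessments or early exposure to DBS could also remove controls. This stands as a caveat. It does not rescue the method: any rule about attending DBS filters one arm, and defining it more precisely does not change that.

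Finally, an instrumental-variable analysis has weaknesses of its own and also reveals the arm. Both are true. The first has to be stated as an assumption, and the second is handled by timing.

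**Conclusion.** The point holds as a weakness in a stated supplementary method. On the natural reading, exclusion falls on the DBS arm alone, breaks the randomised comparison, and is likely but not certain to favour DBS. With assumed non-adherence of 10-30% and an assumed residual gap of 0-0.5 SD, the bias is 0-0.15 SD and null rejection is 5% to about 15.5%. Adjustment for the pre-test score makes the lower part of that range more plausible. It would be wrong to read this as a threat to the trial's main conclusion, since the intention-to-treat analysis is unaffected. The change is a worthwhile, low-cost improvement.

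**What to change.** Keep intention to treat as the basis for inference. Replace the exclusion with a supplementary instrumental-variable analysis (two-stage least squares) with randomised arm as instrument, all randomised dyads kept, and adjustment for baseline score and centre. State one exposure in advance:

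- a binary attendance threshold, giving a complier-average effect; or
- sessions attended, 0-4, reported as a per-session effect under an assumption of linearity.

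Run it after the blinded primary analysis is locked, because attendance data identify the arm.

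**Cost.** This changes analysis wording only. It uses per-dyad adherence records, which the planned exclusion already needs, although the article does not describe how attendance is recorded. Intervals will be wider. The method assumes that allocation acts only through attendance. That needs an explicit caveat, because parents who know their allocation complete the vocabulary checklist (CDI) and may report differently for that reason alone. With a binary threshold, attendance below it must also be assumed to have no effect.

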## Discussion

The Dialogic Book-Sharing programme will be implemented in Italian health, educational and maternal-child centres through the study ‘Early parent–child intervention with Dialogic Book-Sharing: effects on child communicative and socio-emotional development and on parenting’. It will represent an early parent–child intervention in the first thousand days of life and will aim to explore the impact of the DBS method on the child’s linguistic, cognitive, attention and behavioural development in the first 2 years of life, on parent mood (anxiety, depression and stress) and parent–child interactions.

The implementation of the DBS psycho-educational programme in early childhood could enhance the educational resources offered by educational, social and health services, early childhood centres and maternal-child services, in support of parenting and the parent–child relationship. This intervention could represent added value for assistance to families, in terms of the improvement of the psychophysical well-being, the quality of life of the child and their parents, as well as the social well-being of the territory.

The provision of the DBS model has been found to be feasible, acceptable and effective in different ecological contexts and educational services [48, 60, 61, 110]. It represents a strategic opportunity for bringing about positive effects, also in terms of prevention of socio-emotional and cognitive difficulties, and for the promotion of the psychosocial health of the population that attends Italian health, educational and maternal-child centres. As such it represents a promising response to the new social, health and educational needs currently accentuated by the COVID-19 pandemic and the imposition of social isolation adopted by governments to curb the spread of the virus, with consequent adverse impact on the most vulnerable populations [111, 112].

Furthermore, the application of the DBS methodology is also a way to promote the use of books, and thereby counteract the excessive use of technological devices already present in early childhood. In the past decade, screen time has become ubiquitous in children’s daily routines, with an impact across multiple domains of their development [113]: an excessive exposure to screen resulted negatively associated with developmental health outcomes in children [114] since it might harm their cognitive [115], linguistic and social-emotional growth [116].

## Data Availability

The data that support the findings of this study are available from the corresponding author upon reasonable request.

## Abbreviations

ANOVA: Analysis of variance
ANCOVA: Analysis of covariance
ASEBA: Achenbach System of Empirically Based Assessment
CBCL: Child Behavior Checklist
CDI: Communication Development Inventory
COVID-19: Coronavirus disease 2019
DBS: Dialogic Book-Sharing
HADS: Hospital Anxiety and Depression Scale
MNs: Mirror Neuron System
P-CDI: Parent-Child Dysfunctional Interaction
PSI-SF: Parenting Stress Index
RCT: Randomised controlled trial
